#### Nutritional assessment

The Mini-Nutritional Assessment (MNA**®**) is a validated assessment tool for nutritional status [42]. Much of the information required will be collected elsewhere. Additional information that will be collected will include food intake, specifically protein and fruit or vegetable intake, and fluid intake from participant report. Mid-arm circumference will be measured at the mid-point between the olecranon and acromium. Calf circumference will be measured as the widest part of calf. These measurements will be taken for the dominant limb. The MNA (full form) will be assessed at baseline visits and 13 week follow-up visits for each group.

#### Frailty assessment

Frailty will be assessed at first visit, 7 day follow-up, and 13 week follow-up using the Frailty Index (FI) [43], 9-point Clinical Frailty Scale (CFS) [44], and phenotype definition [45]. Activities of Daily Living (ADLs) will be assessed using Katz (basic ADLs) [46] and Lawton (instrumental ADLs) [47] tools. The phenotypic diagnosis of frailty will be made if the participant meets three out of five criteria: low gait speed, low handgrip strength, weight loss, self-reported exhaustion or low physical activity. Cut-offs used in the original phenotype diagnosis will be used for gait speed, handgrip strength, and weight loss. Self-reported exhaustion will be defined if the participant answers “most of the time” or “all of the time” to how often over the last week they had felt that either “everything [they] did was an effort” or they “could not get going” [45]. Physical activity will be defined through self-report by asking the participant if over the last 3 months they have performed no weight-bearing physical activity, been for a short walk once/ month or less, or spent more than 4 hours/ day sitting [48]. The FI will be calculated by counting the total number of deficits present out of 36 defined criteria, and dividing by 36. These criteria have been adapted for secondary care use from those previously validated in a UK community setting to form the electronic frailty index (Supplementary File 1) [49]. The CFS will be determined by the investigating geriatrician after clinical review and after all other information has been collected. The investigating geriatrician will determine this immediately after reviewing the participant by considering ADLs, physical function, self-reported exhaustion, and symptomatic burden reported by the participant.

#### Delirium screening and assessment

Delirium will be diagnosed by the investigating geriatrician as per the Diagnostic and Statistical Manual of Mental Disorders 5 [50]. Participants will first be screened for evidence of delirium at each visit using the Single Question in Delirium “Do you think this patient has been more confused lately?” [51]. The investigating geriatrician will review notes and ask staff caring for the participant, family members, and the participant themselves. The participant themselves will be specifically asked “Has anything strange been happening?”, such as experiencing hallucinations. Where possibility of delirium is raised upon screening or during other assessments, the investigating geriatrician will perform further assessments to formally diagnose delirium by testing attention by months of the year backwards [52], consciousness by the Modified Richmond Agitation and Sedation Scale [53], and cognition by the Abbreviated Mental Test Score (Supplementary File 2).

#### Fluid balance assessment

Fluid balance will be assessed and recorded during all visits during hospitalisation. Fluid balance will be assessed by clinical assessment, review of input/ output charts, and BIA measurements. Clinical assessment by the investigating geriatrician will include review of skin turgor, mucus membranes, oedema, Jugular Venous Pressure level, trends in observations e.g. blood pressure, and patient presentation. The overall fluid status will be recorded as hypovolaemic, euvolaemic, or hypervolaemic for the participant overall. However, if unilateral oedema is present in a single limb this will be recorded. BIA measurements of TBW, ECW, ICW, and third space water will be recorded separately and assessed against all other available information of fluid balance.

### Other outcome data

Further routinely collected data that will be recorded will include (as applicable) the operation performed, peri-operative blood loss, type of post-operative analgesia (patient-controlled analgesia or epidural), postoperative complications, length of stay, discharge destination, other hospital admissions within the 3 month follow-up period, histological diagnosis (cancer vs. not), and 1 year mortality.

### Participant feedback

There is no standardised assessment tool for measuring test acceptability. However, a multi-faceted construct of acceptability has been proposed, which reflects the extent to which people receiving a healthcare investigation or intervention consider it to be appropriate. This construct consists of the affective attitude of the individual, procedure burden, individual ethicality (individual value system), intervention coherence (participant understanding), opportunity costs, perceived effectiveness, and self-efficacy (confidence that they can perform the necessary behaviour) [54]. Considering this construct, we have devised a questionnaire that assesses each of these aspects separately for muscle quantity (for both ultrasound and BIA), handgrip strength, and gait speed testing (Supplementary file 2). These four aspects have been chosen as these will be measured most frequently for all participants in this study and have potential for direct translation into clinical practice. This will be administered to all participants at their final visit.

### Venepuncture (optional)

Blood samples will be taken using the BD vacutainer Safety-Lok™ system in sterile vacutainers without additives (BD biosciences). Samples will normally be taken peripherally but may be taken centrally or via arterial lines if these are in place as part of routine clinical care. Samples will be taken at first visit, and where possible, within 48 h of surgery in the surgical cohorts. Blood samples will be centrifuged within 30 min to 1 hour of collection, within the University of Birmingham Research Laboratories, within QEHB. Serum and plasma samples will be removed using calibrated pipettes and stored at -80 °C prior to further analysis. Serum and/or plasma concentration levels of high sensitivity C-Reactive Protein (hsCRP), Dehydroepiandrosterone sulfate (DHEA-s), cortisol, 25-OH vitamin D, Interleukin 6 (IL-6), Tumour Necrosis Factor Alpha (TNF-α), and Insulin-like Growth Factor (IGF-1) will be measured using Enzyme-Linked Immunosorbent Assays or other appropriate tests. Further additional biomarkers may be tested as appropriate. Remaining serum and/or plasma samples will be stored for use in future ethically approved research within the University of Birmingham Research Laboratories.

### Fitbit inspire physical activity quantification (optional)

The Fitbit Inspire will be applied to the non-dominant wrist during hospitalisation where this is agreed by the participant or consultee. This will record activity statistics during hospitalisation including number of steps taken, distance travelled, and sedentary time. Summary statistics will be recorded for up until 30 days after hospitalisation. Participants will be advised to wear the monitor all the time. They will be supplied with a charger and advised to charge the device every 5 days when at rest, such as at night time. Position changes (e.g. sit to stand) will not be specifically recorded with this device.

### Statistical analysis

#### Power calculation

The sample size for this study has been calculated by considering estimates of the precision of outcomes; 80% power and 5% significance level have been used in calculating this sample size. Allowing for 25% loss to follow-up from a sample size of 56, based on a paired t-test, the following clinically important changes may be detected with a sample size of 45 in each group (all changes are powered to be bidirectional and may be identified at multiple timeframes):
Change of 6 for t-score derived from physical function measured by PROMIS (Mean 50, SD = 10) – from baseline to 1 week and/or from baseline to 13 weeks. This is validated from previous studies [39].Change of 0.66 cm in BATT (Mean 3.6 cm, SD = 1.1 cm) – from baseline to 1 week and/or from baseline to 13 weeks. This is consistent with clinical change detected in our pilot study (mean loss of 0.76 cm) [24].Change of 0.6 in skeletal muscle mass index measured using BIA (Mean 8.5, SD = 1) – from baseline to 1 week and/or from baseline to 13 weeks. This is consistent with change detected in previous studies, consistent with acute sarcopenia [28].Change of 6 kg in handgrip strength (Mean 23, SD = 10) – from baseline to 1 week and/or from baseline to 13 weeks. This is validated from previous studies [37].

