### Design and setting

This is a single site cohort study at the Queen Elizabeth Hospital Birmingham (QEHB), involving 56 elective colorectal, 56 emergency abdominal surgery, and 56 medical patients. QEHB is a large tertiary hospital, with a firmly embedded research infrastructure. In the elective cohort, measurements will be performed in preoperative assessment clinic, within 48 h of surgery, at 7 days postoperatively (+/− 2 days), and at 13 weeks postoperatively (+/− 1 week). In the emergency surgery cohort, we aim to recruit participants preoperatively where possible. Where this is not possible, we will recruit participants within 48 h of emergency surgery; further assessments will be performed at 7 days postoperatively (+/− 2 days), and at 13 weeks postoperatively (+/− 1 week). Medical patients will be recruited within 48 h of admission with further assessment at 7 days post-admission (+/− 2 days), and at 13 weeks post-admission (+/− 1 week). The timeframe of 13 weeks has been chosen pragmatically as a timeframe that was considered important to our patient and public involvement panel that could be feasibly conducted without high drop-out rates. The full study schema is shown in Fig. 1.

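### The power calculation's 56 enrolled, 25% loss and 45 evaluable per cohort cannot all be true: 25% loss from 56 leaves 42

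*Protocol article*

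**What the plan says.** Under Design and setting, the protocol article describes a study "involving 56 elective colorectal, 56 emergency abdominal surgery, and 56 medical patients". The Power calculation section takes the same 56 and applies attrition to it: "Allowing for 25% loss to follow-up from a sample size of 56". It then says that the listed changes "may be detected with a sample size of 45 in each group".

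The calculation is described as "based on a paired t-test", with "80% power and 5% significance level have been used in calculating this sample size" and two-sided testing ("all changes are powered to be bidirectional"). Four detectable changes rest on the 45. Two of them are "Change of 6 for t-score derived from physical function measured by PROMIS (Mean 50, SD = 10") and "Change of 0.66 cm in BATT (Mean 3.6 cm, SD = 1.1 cm"). The other two are 0.6 in the BIA muscle index (SD 1) and 6 kg in handgrip strength (SD 10). Each is claimed for baseline to 1 week, baseline to 13 weeks, or both.

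The section does not say whether the SDs are of a single measurement or of the change, and it gives no correlation between visits.

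**The concern.** The sentence takes the loss from 56, so the evaluable number should be 56 × 0.75 = 42. A gap of 3 is too large for rounding. The 56 is not a misprint, because Design and setting repeats it for each of the three cohorts. Nothing else in the article reconciles the figures, and this is not a detail left to a fuller document, since all three numbers are printed together.

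All four detectable changes, including the one for PROMIS (the primary outcome), hang on the 45. The cohorts are to be analysed separately, and the Discussion relies on the study being powered for within-group differences. The evaluable number per cohort is therefore the figure that supports the sample size. If 42 is the true number, the power attached to those changes needs to be re-examined.

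**Working it through.** **Inputs (all from the protocol article).** Enrolled per cohort: 56. Loss: 25%. Evaluable per group: 45. Power 80%, two-sided 5%, paired t-test. Change divided by listed SD:

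- PROMIS: 6/10 = 0.60
- BATT: 0.66/1.1 = 0.60
- BIA muscle index: 0.6/1 = 0.60
- Handgrip: 6/10 = 0.60

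One standardised change, 0.60 SD, therefore serves for all four.

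**Step 1: attrition.**

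- Evaluable = enrolled × (1 − loss) = 56 × 0.75 = 42.
- Loss implied by 45 of 56 = 11/56 = 19.6%.
- Enrolment needed for 45 after 25% loss = 45/0.75 = 60.
- Adding 25% to 45 gives 45 × 1.25 = 56.25.

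The last line suggests that 45 was multiplied by 1.25 instead of divided by 0.75. That is an inference; the article does not show the step.

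**Step 2: where 45 comes from.** Power is computed from the noncentral t distribution.

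- Two-sample t-test: noncentrality 0.60 × √(n/2), with 2n − 2 degrees of freedom.
- Paired t-test: noncentrality d_z × √n, with n − 1 degrees of freedom. If the listed SD is that of a single measurement, d_z = 0.60/√(2(1 − ρ)), where ρ is the correlation between visits. If the listed SD is that of the change, d_z = 0.60, which is the same as ρ = 0.5.

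| Calculation | n for 80% power | Power at 45 |
|---|---|---|
| Two-sample | 45 | 80.4% |
| Paired, ρ = 0 | 46 | 79.5% |
| Paired, SD of change (ρ = 0.5) | 24 | 97.6% |

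The stated 45 at 80% power is thus reproduced by a two-sample formula, or nearly so by a paired one with no within-person correlation. It is not reproduced by a paired test that treats the listed SDs as SDs of change.

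**Step 3: power at 42 for 0.60 SD.** The article gives no ρ, so the range is shown.

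| Calculation | Noncentrality | Power at 42 |
|---|---|---|
| Paired, ρ = 0 | 0.424 × √42 = 2.75 | 76.6% |
| Two-sample | 0.60 × √21 = 2.75 | 77.6% |
| Paired, ρ = 0.25 | 0.490 × √42 = 3.17 | 87.3% |
| Paired, ρ = 0.5, or SD of change | 0.60 × √42 = 3.89 | 96.7% |

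Paired power at 42 crosses 80% at ρ of about 0.08.

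**Step 4: change detectable with 80% power at 42.** On the two-sample and zero-correlation calculations it is 0.619 and 0.626 SD. Multiplying by the listed SDs gives:

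- PROMIS: 6.2–6.3 (stated 6)
- BATT: 0.68–0.69 cm (stated 0.66)
- BIA muscle index: 0.62–0.63 (stated 0.6)
- Handgrip: 6.2–6.3 kg (stated 6)

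If the listed SDs are SDs of change, the figure at 42 is 0.443 SD, well inside the stated 0.60.

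**The case against.** A reader might infer from the attrition error that the 80% power claim is false and the cohorts are too small. The article does not support that. It names a paired t-test, and for that test 42 falls below 80% only if the correlation between visits is under about 0.08. Repeated measurements on the same person are unlikely to be so nearly uncorrelated. The figures of 76.6% to 77.6% come from calculations the article does not name; they matter only because they reproduce its 45. Even there the loss is about 3 points of power and 0.02–0.03 SD. This objection stands, and the power consequence must be stated conditionally.

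It can also be said that 45 may be the correct requirement and the 25% the mislabelled figure. That is possible too. If 45 was calculated first and 56 obtained by adding 25%, the 45 and its power stand as stated, and only the tolerated loss is wrong (19.6%).

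A third inference, that 45 is missed at every comparison, also goes too far. The article does not say that the full 25% is lost by 1 week, so the 1-week comparisons may retain more than 42.

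None of this reconciles 56, 25% and 45. If the SDs are SDs of change, 24 would suffice and the 45 is unexplained. If they are single-measurement SDs with no correlation, 42 falls short. On neither reading does 25% loss from 56 leave 45.

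**Conclusion.** The inconsistency is certain and needs correcting: 25% loss from 56 leaves 42 per cohort, and 45 of 56 is a loss of 19.6%. Which of the two figures, 25% or 45, is wrong cannot be settled from the article.

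The effect on power is modest at most, and may be nil. On the calculation that yields about 45, power at 42 is 76.6% to 77.6% and the detectable change rises from about 0.60 to 0.62–0.63 SD. Under the named paired test, power at 42 is 80% or more for any correlation above about 0.08. These results assume a two-sided 5% test, the listed SDs and, for the paired results, correlations that the article does not state. The finding is that the sample-size statement contradicts itself, not that the study is underpowered.

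**What to change.** State one consistent set of figures in the Power calculation section. Either of these keeps enrolment at 56 per cohort:

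1. 56 enrolled, 25% loss, 42 evaluable. Restate the power or the detectable changes for 42, and give the SD of change, or the correlation between visits, on which they rest. The values of 0.62–0.63 SD should not simply be inserted, because they hold only on the two-sample or zero-correlation calculation and the section names a paired test.
2. 56 enrolled, 45 evaluable, with the tolerated loss restated as about 20% (11 of 56).

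The cost is a corrected sentence, plus the stated SD of change or correlation under the first option. No extra recruitment is needed, and no procedure or analysis changes. Under the first option the quoted power or detectable change may become slightly less favourable, depending on the correlation assumed. Under the second, the study acknowledges a smaller margin for loss to follow-up.

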### Physical function – patient reported outcome measures information system (PROMIS®)

PROMIS physical function is a validated measure of physical function [39, 40]. PROMIS is an initiative that compares participant responses to a reference population and derives a T-score, where 50 is the mean, and 10 is the standard deviation. PROMIS will be measured at baseline and 3 month follow-up for all groups. The raw scores will be entered into the HealthMeasures scoring service, powered by Assessment Center^SM^ to derive T-scores.

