## Discussion

This study will fully characterise changes in muscle quantity and function in a clinical setting and will provide invaluable information to researchers, clinicians, and patients. The results of this study have potential to lead on directly to further interventional studies to counteract these changes, with particular focus on identified mechanistic associations and clinical factors to guide risk stratification. The results may also lead to direct changes in clinical practice, including the embedding of our research tools into clinical practice, and changes in policy, such as promoting early mobilisation. Providing patients and members of the public with increased knowledge on their risk of declines in muscle quantity and function, and what this is likely to mean for them, can help to empower them in their own decision making and engagement with treatment and therapy.

We recognise that there are a number of limitations of our study. Firstly, this is a single site study, and therefore, the results may not be generalisable to the wider population. Secondly, the cohorts we have included are disease-specific. However, we consider that our results will provide proof of concept, which can be used to guide further research to increase understanding in other disease populations. As described, our study has been powered to detect within group differences in the minimally clinical important differences as derived from other studies. However, this has not been powered separately for gender and other covariates (e.g. cancer vs. not), which may affect measurements. Interim analysis has been planned and our patient and public involvement panel will be involved in the interpretation of these results. At this stage, we will review the overall progress of the study and consider if protocol amendments may be necessary.

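### The stated paired t-test, the quoted SDs and the 45 per group do not fit together; the mismatch is conservative for almost any positive within-person correlation

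*Protocol article*

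**What the plan says.** The Power calculation section fixes the ingredients in one place. The error rates are given by "80% power and 5% significance level have been used in calculating this sample size", and the tests are two-sided, since "all changes are powered to be bidirectional". The test and number analysed are stated as "based on a paired t-test, the following clinically important changes may be detected with a sample size of 45 in each group".

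Four targets follow, for change from baseline to 1 week and/or to 13 weeks:
- PROMIS: "Change of 6 for t-score derived from physical function measured by PROMIS (Mean 50, SD = 10"
- BATT: "Change of 0.66 cm in BATT (Mean 3.6 cm, SD = 1.1 cm"
- Skeletal muscle index by BIA: "Change of 0.6 in skeletal muscle mass index measured using BIA (Mean 8.5, SD = 1"
- Handgrip strength: 6 kg, printed with a mean of 23 and an SD of 10

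The section on PROMIS explains where 50 and 10 come from: the instrument "compares participant responses to a reference population and derives a T-score, where 50 is the mean, and 10 is the standard deviation". The Discussion repeats the within-group purpose: "our study has been powered to detect within group differences in the minimally clinical important differences". No SD of within-person change and no baseline-to-follow-up correlation appears anywhere in the article.

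**The concern.** A paired t-test works on each person's difference, so its sample size depends on the SD of that difference. The SDs quoted here stand beside mean levels (50, 3.6 cm, 8.5, 23 kg), not beside mean changes. For PROMIS the article itself identifies the SD as that of a reference population. For BATT, muscle index and handgrip, the layout suggests the same, but this is inference.

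Four different instruments all give exactly 0.60 SD, and 45 per group is the usual two-independent-sample answer for 0.60 SD. So the named test, the SDs and the number may not come from one calculation.

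At stake is what the study can be said to detect. This is the only sample-size justification shown, and it covers the primary outcome. A reader may take 6 T-score points or 0.66 cm as the limit of detection. Someone reusing the paragraph for another paired study, with the quoted SDs as SDs of change, would plan 45 where 24 would do.

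**Working it through.** **Inputs (Power calculation section).** Power 0.80; two-sided α 0.05; paired t-test; n = 45; recruited 56 with 25% loss.

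**Step 1: standardised targets.**
- PROMIS 6/10 = 0.60
- BATT 0.66/1.1 = 0.60
- Muscle index 0.6/1 = 0.60
- Handgrip 6/10 = 0.60

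**Step 2: try to reproduce 45 (noncentral t).**

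| Calculation at 0.60 SD | n required | At n = 45 |
|---|---|---|
| Paired t, quoted SD taken as SD of change | 23.8, so 24 pairs | power 97.6%; detects 0.427 SD |
| Two independent groups | 44.6, so 45 per group | power 80.4%; detects 0.597 SD |
| Paired t, quoted SD cross-sectional, r = 0 | 45.6, so 46 pairs | power 79.5%; detects PROMIS 6.04 |

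The stated method with the SDs as printed gives 24. The figure 45 is reproduced exactly by the independent-groups test, and to rounding by a paired test with zero correlation.

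**Step 3: if the quoted SDs are SDs of change.** At 45 pairs the detectable changes are 0.427 × SD:
- PROMIS 0.427 × 10 = 4.3
- BATT 0.427 × 1.1 = 0.47 cm
- Muscle index 0.427 × 1 = 0.43
- Handgrip 0.427 × 10 = 4.3 kg

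**Step 4: if the quoted SDs are cross-sectional.** With equal SDs at the two visits, SD of change = SD × √(2(1 − r)), where r is the correlation between a person's baseline and follow-up values. The documents give no r, so the values below are assumptions. Pairs needed for 0.60 SD are 46, 35, 24, 16 and 11 at r = 0, 0.25, 0.5, 0.7 and 0.8.

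The stated 25% loss leaves 56 × 0.75 = 42, where a paired t-test detects 0.443 SD of change. The detectable change is therefore 0.443 × √(2(1 − r)) × SD:

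| Assumed r | √(2(1 − r)) | PROMIS | BATT (cm) | Muscle index | Handgrip (kg) |
|---|---|---|---|---|---|
| 0 | 1.414 | 6.3 | 0.69 | 0.63 | 6.3 |
| 0.3 | 1.183 | 5.2 | 0.58 | 0.52 | 5.2 |
| 0.5 | 1.000 | 4.4 | 0.49 | 0.44 | 4.4 |
| 0.8 | 0.632 | 2.8 | 0.31 | 0.28 | 2.8 |
| Stated in the article | – | 6 | 0.66 | 0.6 | 6 |

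**Step 5: correlation at which the stated claim holds.** Solve 0.60/√(2(1 − r)) = 0.443 for n = 42. Then √(2(1 − r)) = 1.355, 2(1 − r) = 1.836 and r ≈ 0.08. For n = 45, 0.60/0.427 = 1.405, 2(1 − r) = 1.974 and r ≈ 0.013. Power for 0.60 SD at n = 42 is 76.6% at r = 0 and 96.7% at r = 0.5.

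**The case against.** The strongest reply is that the printed numbers are compatible with a paired test. With r = 0 and cross-sectional SDs, 45 pairs have 79.5% power and detect a PROMIS change of 6.04, which rounds to the stated 6. This stands to the extent that the text cannot show which calculation was run. A reader might infer that the wrong test was used, but the documents support only that the inputs disagree as written. It does not rescue the paragraph, because zero correlation between two measurements on the same person is implausible and the article does not state it.

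The second reply is that the article says only that these changes may be detected, not that they are the smallest detectable. This also stands: for almost any positive r the error is on the safe side.

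Third, no planned analysis depends on the paired tests. The primary research question is addressed by models of 13-week PROMIS, and a small observed change would be judged from its estimate and confidence interval. That limits the consequence and is why the severity is moderate.

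Finally, it is tempting to call r = 0 impossible for BATT because the ultrasound section reports intraclass coefficients above 0.9. Those are intra-rater and inter-rater reliability with the same protocol and machine. They are not the correlation between baseline and 1 or 13 weeks after surgery or acute illness, which also depends on how differently patients change.

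**Conclusion.** The point holds as an inconsistency in the stated calculation. A paired t-test at 0.60 SD, 80% power and two-sided 5% needs 24 pairs, not 45, if the quoted SDs are SDs of change. If they are cross-sectional, 45 follows only from an independent two-sample test or, to rounding, from an undeclared r = 0. That the SD is cross-sectional is documented for PROMIS and inferred for the other three measures.

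A reader might conclude that the study is underpowered for the listed changes. The documents do not support that: 42 completers give at least 80% power once r is about 0.08. Nor can it be said unconditionally that smaller changes than those stated are detectable. At r = 0 and n = 42 the detectable PROMIS change is 6.3, slightly above the stated 6; above r of about 0.08 it falls below 6. How far below depends on an r that the article does not give.

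Severity is moderate: the stated basis of the sample size needs correcting, while recruitment and planned analyses do not change.

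**What to change.** Keep 56 per cohort and rewrite the paragraph:

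1. State that the calculation is for a paired t-test and give the SD of change for each outcome, or derive it as SD × √(2(1 − r)) with r stated.
2. For BATT, use the SD of change from the sponsor's pilot if it is available; the article reports only the pilot's mean loss of 0.76 cm. For the other outcomes, and for BATT otherwise, show an explicitly assumed range such as r = 0.3 to 0.8.
3. Report detectable changes at the 42 expected after the stated 25% loss, as in the table under the working.
4. Remove the statement that the four listed changes come from a paired t-test with 45 per group, or declare the assumption that produces it.
5. Do not cite the rater reliability above 0.9 as the value of r.

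The cost is one reworded paragraph and a small table.
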